#### Data validation

A weighted kappa statistic will be used to determine the level of agreement between the patient data in the main study and the validation data. It will also be used to determine the level of agreement between institutional surveys independently completed by the local study lead and one other consultant or registrar at each participating centre. Results will be presented as a proportion of agreement for each variable being validated.

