### Outcome measures

The primary outcome is all-cause, in-hospital mortality.

For patient’s hospitalised for >30 days following primary intervention, a 30-day post-primary intervention mortality rate will be used. Those who do not receive a primary intervention, but remain alive and hospitalised at 30 days following primary admission, will have this time point used for recording their mortality status for the primary outcome. Primary outcome is defined in table 1.

**Table 1 T1:** Generic data points

Generic questions	Answers
During which month did the patient present to your hospital?	October, November, December, January, February, March, April. Please select the month that the patient presented to your hospital for the first time with this congenital anomaly. For example, if a baby was born with gastroschisis on the 29 September and presented to your hospital on 1 October you should select October.
Has consent been provided to include this patient in the study? If no, which condition did the patient present with?	Yes, No, Patient consent is not required for this study at my institution. Oesophageal atresia, Congenital diaphragmatic hernia, Intestinal atresia, Gastroschisis, Exomphalos, Omphalocele, Anorectal malformation, Hirschsprung's Disease. Please select all the conditions that the patient presented with. Do not select a condition which the patient has already received surgical treatment for previously.

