What type of anaesthesia was used for the primary intervention?	General anaesthesia with endotracheal tube, General anaesthesia with laryngeal airway, Ketamine anaesthesia, Spinal/caudal anaesthesia, Local anaesthesia only, No anaesthesia/just analgesia, No anaesthesia/no analgesia, Not applicable: no surgery or intervention undertaken.
Who undertook the anaesthetic for the primary intervention?	Anaesthetic doctor, Anaesthetic nurse, Medical officer, Surgeon, Other healthcare professional, No anaesthetic undertaken. If more than one of these personnel were present, please select the most senior.
Who undertook the primary intervention?	Paediatric surgeon (or junior with paediatric surgeon assisting/in the room), General surgeon (or junior with paediatric surgeon assisting/in the room), Junior doctor, medical officer or other (without a paediatric or general surgeon assisting/in the room), Trainee surgeon (without a paediatric or general surgeon assisting or in the room), Not applicable — no surgery or primary intervention undertaken.
Was a Surgical Safety Checklist used at the time of primary intervention?	Yes, No: but it was available, No: it was not available, Not applicable: a conservative primary intervention was undertaken, Not applicable: no surgery or primary intervention undertaken.
Total duration of antibiotics following primary intervention	In days (including the day of surgery and the day antibiotics were stopped. Include intravenous and oral antibiotics).
Did the patient receive a blood transfusion?	Yes: not cross-matched, Yes: cross-matched, No: not required, No: it was required but not available. Within 30 days of primary intervention or 30 days of presentation if no intervention was undertaken.
Did the patient require ventilation? If yes, for how long did the patient remain on ventilation?	Yes: and it was given, Yes: but it was not available, No. Within 30 days of primary intervention or 30 days of presentation if no intervention was undertaken. Please include all types of ventilation. In days (include all days on ventilation within 30 days of primary intervention or 30 days of presentation if no intervention was undertaken).

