### Data validation

Ten percent of collaborating centres will be selected at random for data validation by an independent research collaborator. The aim will be to determine the numbers of patients eligible during the data collection period to check if any were missed and collect a selection of data again to cross-check for accuracy. Validating questions have been built into the data collection tool. At least 90% of primary and secondary outcomes must be completed for each patient. All collaborators within validating centres will be asked to complete a brief survey regarding their experience with data collection to identify any potential errors and to aid with data interpretation.

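### Validation results are to be presented as a proportion of agreement, which barely registers missed deaths at most HIC mortality rates, and one weighted kappa is applied whatever the variable type

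*Protocol article*

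**What the plan says.** Two parts of the protocol article deal with validation.

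Under Methods and analysis, the Data validation paragraph sets the sample: "Ten percent of collaborating centres will be selected at random for data validation by an independent research collaborator". The validator counts eligible patients to find any that were missed, and is to "collect a selection of data again to cross-check for accuracy".

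Under Data analysis, the Data validation paragraph sets the statistic: "A weighted kappa statistic will be used to determine the level of agreement between the patient data in the main study and the validation data". The same statistic serves the duplicate centre surveys: "It will also be used to determine the level of agreement between institutional surveys independently completed by the local study lead". No distinction is made between binary, nominal, ordinal and continuous items. The paragraph then fixes how results are shown: "Results will be presented as a proportion of agreement for each variable being validated".

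The items in Table 1 are of all four types. The primary endpoint is binary ("The primary outcome is all-cause, in-hospital mortality"). ASA score is ordinal and weight is continuous. Several items are unordered lists, such as mode of transport, type of anaesthesia, cause of death, and who gave the anaesthetic ("Anaesthetic doctor, Anaesthetic nurse, Medical officer, Surgeon, Other healthcare professional, No anaesthetic undertaken").

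**The concern.** Kappa and the proportion of agreement answer different questions. When an event is rare, almost every pair of records agrees because almost every patient survived, so the proportion of agreement is high however badly the deaths themselves are recorded. If that proportion is the presented result, a figure in the high nineties could not vouch for the recording of HIC deaths. The same relative under-recording would lower the figure visibly in low and middle income countries (LMICs). The reading of data quality would then be distorted along the same axis as the study's main comparison.

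A second, separate weakness concerns the weighting. Weighted kappa gives partial credit according to the distance between categories. An unordered list has no such distance, so the value reflects the order in which the options happen to be coded.

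**Working it through.** **Inputs from Table 2.** HIC mortality recomputed from the counts agrees with the printed figures for the five low-mortality conditions:
- oesophageal atresia 6/221 = 2.71% (printed 2.7%)
- intestinal atresia 12/407 = 2.95% (2.9%)
- gastroschisis 28/748 = 3.74% (3.7%)
- anorectal malformation 14/462 = 3.03% (3%)
- Hirschsprung's disease 43/1897 = 2.27% (2.3%)

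The other two HIC figures are higher: 12.7% for exomphalos and 20.4% for diaphragmatic hernia. Combined LMIC figures run from 17.6% to 56.6%.

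**Death: formulas.** Let p be true mortality and s the share of true deaths recorded as deaths, and assume no survivor is recorded as dead.
- Agreement: Po = 1 − p(1 − s)
- Chance agreement: Pe = p·ps + (1 − p)(1 − ps)
- Kappa = (Po − Pe)/(1 − Pe)
- Positive agreement = 2ps/(2ps + p(1 − s)) = 2s/(1 + s), which does not depend on p

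**At p = 3%:**
- One third missed: Po = 1 − 0.01 = 0.990; Pe = 0.03×0.02 + 0.97×0.98 = 0.9512; kappa = 0.0388/0.0488 = 0.80; positive agreement 0.80.
- Half missed: Po = 0.985; Pe = 0.03×0.015 + 0.97×0.985 = 0.9559; kappa = 0.0291/0.0441 = 0.66; positive agreement 0.67.
- All missed: Po = 0.970; Pe = 0.970; kappa 0; positive agreement 0.

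**Across the 2.3–3.7% range:** with half missed, Po runs from 1 − 0.0115 = 98.85% down to 1 − 0.0185 = 98.15%. With all missed it runs from 97.7% down to 96.3%. Kappa is about 0.66 and 0 throughout.

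**Same one-third error at p = 43.7%** (oesophageal atresia, LMIC): Po = 1 − 0.437/3 = 85.4%, against 99.0% above. Pe = 0.437×0.2913 + 0.563×0.7087 = 0.526, so kappa = 0.328/0.474 = 0.69. Positive agreement is again 0.80. Kappa therefore also shifts with mortality, which is why positive agreement or the counts are needed for a fair comparison between income groups.

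**How many HIC deaths would be validated.** Assume that 10% of centres supply 10% of the 183 HIC centre-months (18.3) at the Table 2 monthly case rates. The five conditions give 1.02 + 0.63 + 0.85 + 1.34 + 2.21 = 6.05 cases per month, so 18.3 × 6.05 ≈ 111 patients. Applying the five mortality rates gives about 0.169 deaths per month, or about 3 deaths. Missing all three would still show about 97% agreement.

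**Pooling.** Weighting all seven conditions by Table 2 case rates gives mortality of 5.0% in HICs, 31.3% in LMICs and 18.1% at an assumed 50:50 mix. With half of the deaths missed, agreement is 97.5%, 84.3% and 90.9% respectively.

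**Unordered items: illustrative table, not trial data.** There are four categories A–D and 100 patients. The diagonal holds 40, 20, 20 and 10, and 10 patients are coded A by one source and B by the other. Raw agreement is 0.90.
- Unweighted: Pe = 0.5×0.4 + 0.2×0.3 + 0.2×0.2 + 0.1×0.1 = 0.31; kappa = 0.59/0.69 = 0.855 in every ordering.
- Quadratic weights, codes ordered A, B, D, C: observed mean squared distance 0.10×1² = 0.1, expected 2.7; kappa = 1 − 0.1/2.7 = 0.96.
- Quadratic weights, codes ordered A, C, D, B: observed 0.10×3² = 0.9, expected 3.1; kappa = 1 − 0.9/3.1 = 0.71.
- Over all 24 orderings, linear-weighted kappa runs from 0.78 to 0.92 and quadratic from 0.71 to 0.96.

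For a binary item the choice of weights makes no difference. A 2×2 test table with cells 3, 2, 1 and 94 gives 0.651 unweighted, linear-weighted and quadratic-weighted.

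**The case against.** The strongest reply is that the plan does specify kappa, and kappa responds to missed deaths. A reader might infer that the planned validation cannot show misclassified deaths at all. The document does not support that: the insensitivity belongs to the proportion of agreement, and it matters only to the extent that the proportion is what gets presented. One could also read the last sentence as adding raw agreement beside kappa. That reading is possible, but the sentence names only the proportion as the form of the results, so the wording needs correcting either way.

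Other limits also stand:
- The 2.3–3.7% range covers five conditions in HICs only. In a sample pooled over income groups the masking is much weaker.
- Only a selection of data is re-collected, and the article does not say which items. It cannot be inferred that every Table 1 item is validated, and the contents of the centre survey are in a supplement that is not shown.
- Order dependence needs an unordered item with more than two categories and linear or quadratic weights. The article states no weights. That silence may be settled in a fuller plan and is not itself a fault. The size of the effect above comes from an invented table.
- A reader might conclude that validation could not inform the LMIC–HIC contrast at all. That goes too far: it also looks for missed patients, uses built-in checking questions, sets a 90% completeness requirement for outcomes and surveys collaborators.

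**Conclusion.** The point holds in a limited form. The article fixes a presented metric that is nearly insensitive to missed deaths in five of seven conditions in HICs: 96–99% agreement with half or all deaths missed, against a visible drop for the same relative error at LMIC mortality. It also prescribes one weighted kappa without regard to variable type, which is unsuitable for any validated item with more than two unordered categories.

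The figures for death rest on Table 2 mortality and on the assumption of no falsely recorded deaths. The estimate of about 3 validated HIC deaths further assumes that validated centres contribute in proportion. The code-order range is an illustration only. Neither weakness changes the primary analysis or the sample size, and the weighting issue does not touch death. This is a fault in validation reporting that is worth correcting because the correction costs so little.

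**What to change.** Reword the Data validation paragraph under Data analysis so that:
- kappa with a 95% confidence interval is reported beside raw agreement for each validated categorical item, unweighted for binary and nominal items and weighted, with the weights named, for ordinal items such as ASA score;
- continuous items use an intraclass correlation or limits of agreement;
- for death, the 2×2 counts or positive and negative agreement are given by income group;
- the same matching of statistic to item type applies to the duplicate centre surveys.

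The cost is a few sentences and a few lines of code, with no new data. The intervals for HIC deaths will be wide because few such deaths will be validated. Reporting them openly is still more informative than a single high percentage.

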### Patient and public involvement

CDH UK, a patient and family advisory group and charity, provided input into the design of the study protocol and data collection tool. Their input will be sought on the findings and dissemination of the results.

## Ethics and dissemination

### Research ethics approval

The study has been classified as an audit at the host institution and hence did not require ethical approval. The study fulfils the audit criteria as follows: (1) All data collected measures current practice. The study does not involve any changes to patient management. (2) Current practice and outcomes in low, middle and high income countries will be compared with published standards in the literature. Table 2 details the current mortality standards for each of the seven study conditions in high income countries. (3) All the study data are routinely collected information which should be known to the study team without asking additional questions to the patients/parents. (4) All data to be entered into REDCap are entirely anonymous. (5) No individual patient, collaborator, institution or country will be independently identifiable in the study results. (6) All data will be stored securely and will be governed by King’s College London data protection team.

Research collaborators were required to gain approval to participate in the study at their institution according to their local ethical regulations. Data transfer agreements were legally signed between institutions where required. The participating institutions, type of study approval and study approval reference numbers are detailed in online supplementary file 3. It was not mandated for study approvals to be translated into English. Hence, some reference numbers are in the local scripture of the participating country and have therefore not been incorporated into the table.

10.1136/bmjopen-2019-030452.supp3Supplementary data

### Study dissemination

The study concept and design will be presented at international conferences in order to recruit collaborators. Following completion, the results will be presented at local, national and international conferences globally. Both the promotional presentations of the study protocol and the study results will be presented by study collaborators of all levels of training, disciplines and regions of the world. The results will be submitted for open access publication in a peer reviewed journal. Following publication, the full anonymous, deidentified dataset will be made publicly available via an online repository. Collaborators will have the opportunity to undertake sub-analyses of the data for their country (if all collaborators from that country agree), region or continent.

## Discussion

This study aims to define, for the first time, the management and outcomes of a selection of common life-threatening congenital anomalies across the globe. This will help to raise awareness of the unacceptable disparities in outcomes between low, middle and high income countries and the need to focus on improving access to quality surgical care for neonates with congenital anomalies within national health plans and global health prioritisation. It is hoped that factors affecting mortality and morbidity will be identified that can be modified to improve care. Establishment of the Global PaedSurg Research Collaboration developed during this study will create a platform for ongoing collaborative work and interventional studies aimed at improving outcomes in the future.
